**Background:**

Major intervention programs have been launched, which use mass drug administration (MDA), often given annually and over protracted periods, to control STH. However, the evidence base is lacking on how effective MDA can be and whether it might result in the emergence of pathological conditions, as helminth infections are thought to have profound effects on the immune system.

Parasitic helminths have strong immunomodulatory activities affecting responses to third party antigens. In many parts of the developing world, malarial and helminth infections are co-endemic and many children are infected by both parasites. Investigation on the immunological associations between helminth infections and malarial parasites in co-endemic areas hold the key to answer the question whether helminths increase suppressory immune responses and increase susceptibility to malarial parasites on the one hand but protect from cerebral malaria on the other. Indonesia is a country in transition from one with high burden of infection and traditional lifestyle to one where infectious diseases will be controlled and modern lifestyle will take over bringing along an increase in inflammatory diseases such as allergies. So far most studies analyzing the effect of helminths on immune responses, malaria or allergies have been cross sectional. There are only two recent longitudinal study of the effect of anti helminths on allergy with a randomised placebo controlled design and none studying malaria outcomes; such studies are needed to establish the role that helminths play in suppressing immune responses and affecting malaria or allergies. For co-infections with malarial parasites, detrimental or protective effects of helminth infections will change policies regarding helminth control programs as would information on the mechanistic pathways such as immune responses that can provide valuable information for vaccines and drug design that aim to control infection or disease. Equally important is the results generated from studies involving the effect of helminths on inflammatory diseases such as allergies. These are diseases of populations with Western life style and as Indonesia is moving rapidly towards stronger economy and consequent increased urbanisation and adoption of Western life style, this program is getting prepared for what are expected to form serious future public health problems. The global initiative to control helminth infections worldwide is based on assumptions that these infections affect child health. Growth and cognition are thought to be adversely affected. However, a recent review challenges the consistency of such findings.

Altogether, well-controlled randomised trials are needed to provide us with robust data regarding the effects that helminth infections have on health and disease.

**Trial objectives and purpose:**

- To assess the effect of albendazole on prevalence of malarial parasitemia and on fever and malarial-like symptoms.
- To assess the effect of albendazole on prevalence of SPT reactivity to allergens and symptoms of allergy.
- To assess the effect of albendazole on prevalence of soil-transmitted helminths.

**Trial design**

Household-based cluster-randomized, double-blind, placebo-controlled trial. Household clustering will be used in order to maximally interrupt the transmission of helminths.

**Trial Endpoints**:

***Primary outcomes***

- prevalence of malarial parasitemia
- prevalence skin prick test (SPT) reactivity to allergens
- prevalence of soil-transmitted helminths

***Additional outcomes***

- fever and additional malaria-like symptoms
- symptoms of allergy
- body mass index

**Trial treatment:**

Albendazole (400 mg) and identical pill as placebo were manufactured by PT Indofarma Pharmaceutical, Bandung, Indonesia. The treatment will be provided every three months for a period of 21 months after the start of treatment.

**Randomization and blinding**

The houses will be marked by Global Positioning System (GPS) system to allow maps to be generated using ARC GIS 9 software (ESRI, USA). Individual’s geographical coordinates will be assigned as well as centre coordinates for households. Computer-aided block randomization by household, using Random Allocation Software will be used to assign treatment groups. The treatment will be coded as A or B and the code will be concealed from investigators and patients. Labels with the study subject ID will be printed from a computer database and attached to the appropriate strip of treatment by the study team located in Jakarta without the involvement of the field study investigators.

A number of nested studies will be conducted which will also use the Random Allocation software to apply to the treatment A and B arms and generate within each of these arms, sub samples for cellular immunological study. The treatment code will be de-blinded when all data needed for analyses are entered into the database.

**Selection of study subjects**

***Inclusion criteria***

Subjects of both sexes, aged 2 years and older, in good health, without any clinical condition requiring chronic medication and who have given informed consent (written or thumb print) will be recruited into the trial.

***Exclusion criteria***

Children younger than 2 years of age

Pregnant women

Subjects with clinical condition requiring chronic medication

No informed consent

### Procedures for collection of samples

**Methods and timing of assessments**

***Malaria parasite assessment by microscopy***- at pre treatment and at 3, 6, 9, 12, 15, 18 and 21 months after the start of treatment.

Thick and thin blood smears will be prepared from finger prick blood. The slides will be stained with Giemsa and examined microscopically for all species of malaria parasites according to WHO SOP. The technicians reading the malaria slides will be certified at the US-Naval Medical Research Unit #2 (US-NAMRU2) in Jakarta. The outcome will be positive or negative to assess prevalence.

***Malaria parasite assessment by Polymerase Chain Reaction (PCR)-*** at pre treatment and at 9 and 21 months after the start of treatment.

Blood kept frozen (at -20o C) will be used for DNA extraction and analysis by PCR according to published protocols ([name] et al., BMC Infect Dis. 2010 Mar 25;10:77 and Hamid et al., BMC Infect Dis. 2011 Apr 1;11:83). The test will be undertaken at LUMC.

***Helminth parasite assessment by microscopy***- at pre treatment and at 9 and 21 months after the start of treatment.

Stool containers will be distributed and collected by health workers and delivered to the field laboratory. Technicians trained and certified in Jakarta will perform the microscopic examination of the stool samples ([name] et al., BMC Infect Dis. 2010 Mar 25;10:77 and Hamid et al., BMC Infect Dis. 2011 Apr 1;11:83).

***Helminth parasite assessment by PCR***- at pre treatment and at 9 and 21 months after the start of treatment.

Fresh stool samples will be kept frozen (at -20o C) and used for DNA extraction and analysis by PCR to detect *Ascaris lumbricoides, Necator americanus and Ancylostoma duodenale* as well as *Strongyloides stercoralis*, according to published protocols ([name] et al., BMC Infect Dis. 2010 Mar 25;10:77 and Hamid et al., BMC Infect Dis. 2011 Apr 1;11:83). The test will be undertaken at LUMC.

***Fever and additional malaria-like symptom registration*** by questionnaires designed based on WHO recommended criteria at monthly visits by trained health workers. Fever will be measured by assessing oral temperature using digital thermometers.

The forms to record fever and additional malaria-like symptoms are appended (see appendix 1), will be used by trained health workers at monthly visits to households. Each health worker will be responsible for 20 houses. History of fever, malaria like-symptoms, health care visits and medications used are recorded within one month period. Individuals with fever and/or additional malaria-like symptoms within two days and at the time of visit are referred to the local primary health center (Puskesmas) for further assessment.

***Skin prick testing***- at baseline pre treatment and at 9 and 21 months post treatment assessed by one investigator. The skin prick testing (SPT) to allergens *Dermatophagoides pteronyssinus* and *farinae*, *Blatella germanica* is performed according to protocol published (Hamid et al., BMC Infect Dis. 2011 Apr 1;11:83). The study of allergic outcomes aims to look at school-age children and therefore this test will be restricted to school-age children in our study households.

***ISAAC questionnaire administration***- at baseline pre treatment and at 21 months after the start of treatment by one investigator

The ISAAC questionnaires developed specifically for study area during EU funded project GLOFAL ([www.glofal.org](http://www.glofal.org/)) will be used along with visual material to assess the prevalence of reported allergic symptoms (Asthma, Rhinitis and Eczema).

The study of allergic outcomes aims to look at school-age children and therefore this test will be restricted to school-age children in our study households.

***Anthropometry assessment***-at baseline pre treatment and at 9 and 21 months after the start of treatment.

Height and weight will be measured using scales (standard SECA tools).

***Blood sampling-*** at baseline pre treatment and at 9 and 21 months post treatment, 6 mls of peripheral blood collected into heparin tubes (BD vaccutainers) by experienced medical staff for use in immunological work. Plasma samples will be separated for measurement of antibody levels

**Assessment of adverse events**

Although albendazole is a well established safe drug, the study population will be informed to report any adverse reactions to field physicians and health workers. Adverse events spontaneously reported by the patient or observed by the investigators, will be monitored throughout the study. The reports will be sent to safety clinician responsible for adverse events reporting and assessed whether it is a trial related adverse event.

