**Appendix 1**

**The forms to record fever and additional malaria-like symptoms**

Date of Visit: ___ ___ . ___ ___ . ___ ___ ___ ___

Name of Subject: _________________________________ Subject ID: ___ ___ ___ ___

Village: ___ Household: ___ ___ ___ Name of Cadre: _______________

1. **Was subject ill since last visit ?** ⁮ Yes ⁮ No

1a. **Symptoms:**

⁮ Fever (including Chills and Sweating)

⁮ Headache

⁮ Fatigue (including Myalgia and Arthralgia)

⁮ Vomiting

⁮ other (specify): _________________

1b. **How long ago ?** _____ days ago / ⁮ currently ill?

1c. **Duration of symptoms** : _____ days

1d. **Temperature (if fever or history of fever):** _________ °C

2. **Did subject take treatment for illness ?** ⁮ Yes ⁮ No

2a. **Who gave treatment ?** ⁮ self-medication ⁮ puskesmas ⁮ doctor ⁮ other

2b. **Name of drug (incl. traditional herbs)**: ___________________________________________

3. **Did subject visit health care center since last visit ?**  ⁮ Yes ⁮ No

3a. **Which ?** ⁮ puskesmas ⁮ doctor ⁮ hospital ⁮ other

3b. **Date of visit:** ___ ___ . ___ ___ . ___ ___ ___ ___

3c. **hospitalized?** ⁮ Yes ⁮ No

4. **Notes:**

|  |
| --- |

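### The adverse-event section does not name the monthly symptom form as a source, so a hospitalisation recorded on it is not required to reach the safety clinician

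*Protocol*

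**What the plan says.** The Assessment of adverse events section of the protocol is one short paragraph with three working parts.

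- Participants are told what to do: "the study population will be informed to report any adverse reactions to field physicians and health workers".
- The events to be followed are described: "Adverse events spontaneously reported by the patient or observed by the investigators, will be monitored throughout the study".
- The route is given: "The reports will be sent to safety clinician responsible for adverse events reporting and assessed whether it is a trial related adverse event".

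Methods and timing of assessments sets up a separate contact with every household. The form for fever and malaria-like symptoms "will be used by trained health workers at monthly visits to households", and its scope is stated as "History of fever, malaria like-symptoms, health care visits and medications used are recorded within one month period". People with fever or malaria-like symptoms at the visit or within two days of it "are referred to the local primary health center (Puskesmas) for further assessment".

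The form itself is in Appendix 1. It carries a subject ID and opens with "Was subject ill since last visit". It has tick boxes for fever, headache, fatigue and vomiting, and a free-text box for other symptoms. It then asks about treatment taken, health care visits and, at item 3c, whether the subject was hospitalised.

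The Data management section has a study investigator inspect and approve these forms before two trained staff enter them.

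**The concern.** The trial has two channels of information about illness, and the text does not join them. The adverse-event channel waits for someone to volunteer or notice an event. The monthly form asks every subject in both arms the same questions under blinding, and some of its items, hospitalisation above all, are what a safety clinician would want to see. Yet the adverse-event section does not name the form, and the description of the form does not mention adverse events.

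The participants are in good health, may be as young as 2 years (Inclusion criteria), and receive albendazole or placebo every three months for 21 months (Trial treatment). The Background asks whether mass treatment could lead to pathological conditions. In that setting a hospitalisation should not depend on someone choosing to report it a second time. Two things are at stake: prompt review of a serious event in an individual, and the completeness of whatever the trial later says about harms.

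**Working it through.** The point rests on no stated figure, so the check is a comparison of sections, asking at each step whether the text creates a duty to report.

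1. **Which events the adverse-event section covers.** Those volunteered by participants or observed by investigators. No scheduled question about adverse events appears in this section or elsewhere in the protocol.

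2. **What goes to the safety clinician.** The reports. In context these are the reports of the events just described. The monthly form is not named.

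3. **What the monthly form collects.** It is completed per subject, in both arms. The symptom boxes follow from a positive answer to the illness question. The health care visit question is a separate numbered item, and hospitalisation is a sub-item of it. A hospitalisation is thus recorded whether or not the symptom boxes point to malaria.

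4. **What follows from a form entry.** The one stated action is referral to the primary health centre. It applies to fever or malaria-like symptoms, and only around the time of the visit. The form looks back about one month. Taking a month as 30 days, a two-day window covers 2/30 = 7% of the look-back period, or 3/30 = 10% if the day of the visit is added. These are shares of days, not of events. They show that most of the recall period lies outside the referral rule. In any case the referral goes to the health centre, not to the safety clinician.

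5. **What the investigator's inspection adds.** It is described under Data management as a step before data entry. No safety action is attached to it.

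6. **A test case.** A subject is hospitalised two weeks before a visit and is well on the day. The health worker marks item 3c yes. There is no current or recent fever, so no referral follows. An investigator approves the form, and it is entered. Every written instruction has been followed, and the safety clinician need not have heard of the event.

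The gap is therefore in the routing. The information is collected and reaches the database, but no sentence classes it as adverse-event information or sends it on.

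No loss of power or precision is calculated. The documents give no capture rate for spontaneous reporting and no expected rate of any harm. The form items are also recorded for both arms, so a later comparison by arm on those items loses nothing through the wording of the adverse-event section.

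**The case against.** The case on the other side is substantial.

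- *The section is not exclusive.* It says that reported or observed events will be monitored and does not say that others will be ignored. A reader might infer that events count only if volunteered or observed. The text does not go that far. What stands is that the form is not named as a source.

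- *Investigators see every form.* A hospitalisation marked on an inspected form could fairly be treated as observed by an investigator. That reading is possible, and it means that somebody on the team looks at the entry. But the text does not require that reading, and the inspection is described only as preparation for data entry.

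- *Reporting is less passive than it sounds.* Health workers are named recipients of reports and visit monthly, so each household has a regular occasion to speak up. This reduces the expected shortfall but does not ensure that a form entry is passed on.

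- *The form is not confined to the malaria outcome.* A reader might infer that it serves only that purpose. No sentence limits its use, and it records health care visits, medication and hospitalisation as well.

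- *No safety endpoint is planned.* Harms are not among the objectives or listed outcomes, and tabulation by arm is commonly left to the analysis plan, which is not at hand. This is a fair reason to rate the point low. It does not answer the routing question, because who is told of a hospitalisation is a field procedure and belongs in the protocol.

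- *Vomiting is already an outcome item.* It is listed among the symptoms on the malaria form, so treating it as a harm makes one tick serve two purposes. This is correct, and the amendment has to deal with it.

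**Conclusion.** The concern holds as a minor point and a cheap improvement. The protocol bases adverse-event monitoring on spontaneous reports and investigator observation. It does not name the monthly form as a source, and it nowhere requires a recorded hospitalisation to reach the safety clinician. A hospitalisation could therefore be entered as data without safety review, and harms are likely to be incompletely captured.

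A reader might go further and conclude that harms are in fact under-counted in this trial, or that its ability to detect a difference in harms falls by a stated amount. The documents support neither. Incomplete capture is the usual expectation with unprompted reporting, but nothing here measures it. Any power figure would rest on invented capture rates and event risks, and could not apply to items that both arms already have in the database.

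The conclusion assumes that no field procedure outside this document already forwards hospitalisations. If one exists, citing it in the protocol would settle the matter.

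**What to change.** Amend the Assessment of adverse events section in three respects:

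1. Name the monthly form as a source of adverse-event information alongside spontaneous reports and investigator observation.
2. Require every positive answer to the hospitalisation item, and any relevant free-text symptom entry, to be forwarded to the safety clinician. The investigator's existing inspection of the forms is a natural point for this step.
3. State that these items will be tabulated by coded arm (A or B), which does not break the blind, and that vomiting also belongs to the malaria-like symptom outcome and is reported as such, so that the overlap is visible.

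A further question on the form about reactions since the last tablet is optional, and the point does not depend on it.

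The cost is a few sentences. Visits, forms, inspection and data entry are already in place. The downside is more reports for the safety clinician to review, many of which may turn out to be ordinary illness.

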**Data management**

The database will be designed in MS Access and managed at LUMC but the latest database will be sent to the PI in Indonesia at weekly intervals as read only file. All data collected in the field at the monthly follow ups of fever and additional malaria-like symptoms will be entered by two trained data entry personnel after the forms are inspected and approved by study investigator. For each data series, procedure for double entry, quality control and coherence queries procedures will be implemented systematically in order to detect errors and/or missing data. After integration of all the data corrections on the whole data base, the data base will be locked and saved before it is transferred to the trial statistician. Each step of the process will be controlled by implementation of individual passwords and/or regular back-ups, in order to allow access to the data base and to ensure its integrity.

**Confidentiality of individual data**

Participant confidentiality will be strictly safeguarded by the participating investigators and their staff. This confidentiality is extended to cover testing of biological samples and possible future genetic tests in addition to the clinical information relating to participants. The study protocol, documentation, data, and all other information generated will be held in strict confidence. No information concerning the study or the data will be released to any unauthorized third party.

**Statistics**

***Sample size calculation-*** The sample size calculation document was prepared by statisticians from LUMC and is provided in a document in appendix 2.

#### Analyses of Trial data- The LUMC will conduct the analyses of trial data for manuscripts approved by the publication committee. At a minimum, the trial manuscripts are expected to address the primary and secondary outcomes as well as the additional outcomes listed in the protocol.

***Statistical methods***- The appropriate statistical methods for longitudinal data and repeated measurements will be used. As the data are very complex, appropriate modeling will be needed in close collaboration with biostatisticians at LUMC to analyze the data.

**Laboratory methods**

The laboratory methods used have been published in 2 protocol papers. ([name] et al., BMC Infect Dis. 2010 Mar 25;10:77 and Hamid et al., BMC Infect Dis. 2011 Apr 1;11:83).

**Quality control**

Several measures will be taken to assure a high level of quality control in all aspects of the study.

Questionnaires: health workers will attend regular training sessions to be trained and re trained by study investigators in order to keep to standard administration of questionnaires that record malaria-like symptoms.

All pipettes will be calibrated twice a year at LUMC and returned to the field laboratory.

The technicians conducting malaria and helminth assessment will be trained and re trained in Jakarta and in the field twice a year.

Double entry of selected fields will be undertaken, to assure that errors in data entry are minimized and the final dataset is as clean as possible.

**Supplies**

All supplies needed for the study not available in Jakarta will be shipped from the Netherlands to Jakarta and from Jakarta to Ende. The supplies will be the same (ie same company and product number) throughout the study.

The checklist of reagents will be drawn every 3 months and orders will be placed by fax or email (if internet connection works properly).

Storage room will be checked and lists will be updated at one monthly interval with study investigators being responsible for the updates.

